**Secondary outcomes**						
	Navigator satisfaction: NAVSAT Pt 1		✓			
	Client intervention satisfaction: Study Participant Feedback Questionnaire	✓	✓		✓	
	PrEP care continuum (accepted, initiated, and adhered): navigator report, medical record, and self-report		✓		✓	
	Substance use treatment continuum (accepted, initiated, and adhered): navigator report, medical record, and self-report		✓		✓	
	Linkage to other services: self-report and Navigator report		✓		✓	

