#### Pilot Intervention Navigation Protocol

The navigation process will be informed by evidence-based practices from NAV, including harm reduction, peer navigation, motivational interviewing, and prevention care management to navigate reentry back into the community (eg, referrals for mental health treatment, substance use treatment, and social services) [20]. Navigation processes will be informed by 2 cascade frameworks: the *PrEP Continuum of Care* model [49] and the *Juvenile*
*Justice*
*Behavioral*
*Health Services*
*Cascade* [50]. The PrEP continuum emphasizes identifying individuals at risk for HIV acquisition, increasing awareness of and willingness to take PrEP, ensuring linkage and access to PrEP, and adherence to PrEP medications. The *Juvenile Justice Behavioral Health Services Cascade* [50] was developed to move CLI youth from substance use screening and identification in CL settings to community-based treatment initiation and engagement; this cascade will be adapted to reflect processes specific to YAs.

Navigators will act as role models who can steer participants through the upstream steps of these cascades from screening to linkage with an exploratory look at engagement or initiation, adherence (PrEP specific), and continuing care (substance use treatment) or persistence (PrEP specific). We will test a 30-day intervention period (Textbox 1 for sample navigator visits, adapted from *NAV*). The first session (~75 minutes) will occur within 5 days of referral. In line with the *NAV* protocol, the navigator will initiate contact with the participant ≥3 times per week after the first session (the number of contacts may be higher, depending on the participant’s needs and desires) [20]. Additional contacts could be made throughout the 30-day period in-person or with support via Chorus (eg, SMS text messages). Visits can occur via Zoom, telephonically, or in person based on the participant’s preferences. To maximize program retention, each navigation session will begin by updating the participant’s contact information. If detention interrupts intervention delivery, we will “reset,” where the participant left off to complete 30 days of exposure. Intervention “graduation” will be acknowledged and included in each participant’s action plan (eg, certificate of completion).

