#### Open Pilot Outcomes

In addition to completing a 7-day minimum navigator training, the open pilot’s primary outcome is qualitative feedback to assess appropriateness and satisfaction. The results will be used to refine the intervention for pilot testing in aim 3.

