#### Data Collection

The baseline assessment will occur immediately following participant consent, prior to randomization, and follow-up assessments will occur at 1 month and 3 months (Figure 3). Data will be collected via face-to-face one-on-one interviews in private locations to ensure confidentiality. If face-to-face interviews are not possible, a participant will be given the option of completing the assessment via a secure web-based survey link. Regardless of the method of interview administration, REDCap will be used to collect data (ie, in person on tablets or via a secure REDCap survey sent via email). If completing the assessment via a secure link, specific instructions will be provided to the participant to inform them about how to keep their data private.

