#### Pilot Trial Outcomes

Primary outcomes are linkage to substance use treatment and PrEP services. Because PrEP and substance use treatment health service linkage are a process and not a 1-time event, we will also explore prelinkage (eg, navigator satisfaction) and downstream outcomes (eg, PrEP initiation, adherence, and substance use treatment continuing of care) in an exploratory fashion [55]. The navigator will track these outcomes, but the primary outcomes of (1) PrEP linkage will be attendance at a PrEP services appointment, verified by medical records and (2) substance use treatment linkage will be attendance at a substance use treatment appointment, verified by the navigator and medical provider collateral (if the participant agrees). Other exploratory outcomes include time to health service linkage (substance use and PrEP) and data on HIV testing at the PrEP linkage appointment (uptake, result). Participants will be asked whether and for how long they have experienced hospitalization, residential treatment, and detention since the intervention to account for any system barriers to linkage. We will also assess preferred methods for communicating with the navigator as well as participant satisfaction with the intervention and navigator services. Table 1 provides additional detail on outcomes and correlates.

**Table 1 table1:** Description and schedule of outcomes from a 90-day randomized controlled trial designed to link young adults impacted by the criminal legal system to substance use and HIV prevention services in Allegheny County, PA.

Primary outcomes		Baseline		30 days		90 days
PrEP^a^ linkage: medical record				✓		✓
Substance use treatment linkage: self-report, medical provider collateral if the participant agrees				✓		✓

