#### Data Management and Analysis

REDCap will facilitate routine data checking and exportation of data for analysis. Analyses will be conducted using SAS (version 9.4; SAS Institute). Preliminary analyses will include the examination of descriptive statistics, distributions, and internal consistency reliability of scaled measures. Logistic regression will be used to examine the relationship between the condition and the primary outcomes (services linkage, ie, PrEP, substance use treatment), and all other dichotomous outcomes (eg, acceptance of PrEP and substance use treatment referral). Dependent variables in initial analyses will be summary dichotomous indicators based on both month 1 and 3 assessments, reflecting whether the outcome ever occurred. Subsequent analyses will separately examine whether outcomes occurred by month 1 and by month 3. Generalized linear models will be used to examine variously distributed continuous outcomes (navigator contacts, time-to-service linkage, and satisfaction). Exploratory analyses will build on these models to preliminarily examine the impact of potential moderating variables including sociodemographic characteristics, HIV risk behaviors and perceptions, PrEP-related knowledge and attitudes, substance use treatment behaviors, psychiatric symptoms, social support, and substance use on primary and secondary outcomes.

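### Navigator report is a 30-day and 90-day source for three secondary outcomes, but the only stated navigation period is 30 days and controls appear to have no navigator, so ascertainment may differ by time and by arm

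*Protocol article*

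**What the plan says.** The duration of navigation appears once in the protocol article, under aim 2, Pilot Intervention Navigation Protocol: "We will test a 30-day intervention period". On timing, the same section says "The first session (~75 minutes) will occur within 5 days of referral". If detention interrupts delivery, navigation resumes "where the participant left off to complete 30 days of exposure", and the course closes with a graduation. Open Pilot Outcomes then says "The results will be used to refine the intervention for pilot testing in aim 3". The aim 3 text gives no duration of its own.

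For aim 3, Data Collection states that "follow-up assessments will occur at 1 month and 3 months". In Table 1, three secondary rows are ticked at both 30 and 90 days with navigator report among their sources:

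- "PrEP care continuum (accepted, initiated, and adhered): navigator report, medical record, and self-report"
- the substance use treatment continuum, with the same three sources
- linkage to other services, with self-report and navigator report only

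Pilot Trial Outcomes adds "The navigator will track these outcomes", with no end date. Standard of Care describes the control condition as a case worker's referral. Data Management and Analysis compares dichotomous outcomes by condition with logistic regression, first as ever occurred, and then: "Subsequent analyses will separately examine whether outcomes occurred by month 1 and by month 3".

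**The concern.** An outcome source should be equally available at each time point being reported and in each arm being compared. Navigator report seems to meet neither condition.

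Over time, the navigator is in frequent contact during the stated 30 days, and the article does not say what the navigator can observe from then to day 90. Between arms, a step known only to the navigator can be counted for an intervention participant but, as far as the article shows, not for a control.

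The pilot is meant to inform a larger trial, for which it matters whether the intervention moves people along the care continuum and whether this continues after navigation stops. If one arm has an extra source that is fuller early than late, the month 1 and month 3 contrasts mix real effect with ascertainment.

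**Working it through.** **Inputs.** Navigation: 30 days, with the first session at most 5 days after referral (aim 2, Pilot Intervention Navigation Protocol). Follow-up: 30 and 90 days (Table 1). Arms: 50 intervention and 25 control (Recruitment and Randomization). The article gives no figure for ascertainment, so there is no plan figure to reproduce.

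**Coverage of follow-up by an uninterrupted course, taking referral as day 0.**

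- Start on day 0: 30/90 = 33% of follow-up is covered, leaving 90 − 30 = 60 days (67%) uncovered. This is 30/30 = 100% of the first 30 days and 0/60 = 0% of the rest.
- Start on day 5: navigation ends on day 35, and the span to that day is 35/90 = 39% of follow-up. Navigation covers 25/30 = 83% of the first 30 days and 5/60 = 8% of the remaining 60.
- A detention pause moves the end later by the length of the pause.

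**Sources by row if the navigator has no view after navigation ends.**

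| Row in Table 1 | Listed sources | Left late in follow-up |
|---|---|---|
| PrEP continuum | 3 | 2 (medical record, self-report) |
| Substance use treatment continuum | 3 | 2 (medical record, self-report) |
| Linkage to other services | 2 | 1 (self-report) |

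**Effect on the between-arm contrast.** Assume that a step counts if any listed source shows it. Let p1(t) and p0(t) be the proportions in the intervention and control arms with a step by time t, as found from the other sources. Let n1(t) be the further intervention-arm proportion known only to the navigator. The observed difference is

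[p1(t) + n1(t)] − p0(t) = [p1(t) − p0(t)] + n1(t), with n1(t) ≥ 0.

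With no navigator for controls, there is no matching n0(t). The extra term favours the intervention at both time points. If the navigator's view ends at about day 30, new navigator-only steps stop accruing then, while steps in both arms still accrue through the other sources. The change from month 1 to month 3 is then partly a change in ascertainment. No value of n1(t) can be obtained from the article.

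**Other text on when navigation ends.** Navigator satisfaction has a single tick, at 30 days, and participants are asked about hospitalization, residential treatment and detention after the intervention. Both fit navigation ending before day 90. The 90-day label on the session-content box describes the trial, not the navigation.

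**The case against.** The strongest reply is that the 30 days belongs to aim 2, that the intervention may be refined before aim 3, and that the aim 3 schematic (Figure 3) is not shown and may give a duration. This stands as a reason to ask for reconciliation rather than to assert an error. It does not remove the problem, because the text offers no other duration.

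A reader might infer that either the navigator source stops at day 30 or navigation really runs 90/30 = 3 times as long as stated. The documents do not support that either/or. The navigator could go on recording outcomes without delivering navigation, and a detention pause can put contact after day 30. That third reading is itself unstated. The follow-up contacts in the session-content box also include ongoing support, so tracking through participant contact would be hard to separate from exposure.

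A reader might also expect a spurious fall in the intervention arm between month 1 and month 3. The planned outcomes are cumulative, so a step counted by month 1 stays counted. This part of the reply is right for the within-arm proportion. It does not protect the between-arm difference, which can still shrink or be inflated.

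It is tempting to put a count on the loss. If 20–30% of the 50 intervention participants took a step after day 30, and the other sources captured 60–80% of what all sources would, the loss would be 0.20 × 0.20 = 4% to 0.30 × 0.40 = 12%, or 2 to 6 people. Both rates are assumptions with no basis in the article, so this is not an estimate. Nor does the article date initiation or adherence, so it cannot be said that most such steps fall after day 30.

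Finally, the stakes are limited. The text treats downstream steps as exploratory, and both continuum rows keep two other sources at 90 days.

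**Conclusion.** The point holds as an ascertainment problem in three secondary rows of Table 1. Navigator report is a source at 30 and 90 days. The one stated navigation period covers 33% of follow-up, or runs to 39% with the latest start and no pause. Contact and reporting after that are undefined. The source also appears to exist in the intervention arm only, and this applies at 30 days as well as at 90.

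Month 1 and month 3 comparisons by condition on these rows may therefore be distorted. The one-arm source pushes the difference towards the intervention, and its likely fading after about day 30 blurs the change over time. The size is not derivable from the document.

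This rests on three assumptions: the 30 days carries over to aim 3, controls have no navigator, and a step counts if any listed source shows it. PrEP linkage as a primary outcome is verified by medical records and is not affected. The change is worth making because it is cheap, but the planned primary PrEP analysis does not depend on it.

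**What to change.** 1. Reconcile the aim 2 Pilot Intervention Navigation Protocol, the aim 3 Pilot Trial Outcomes and Table 1 on whether navigator contact and navigator reporting continue after day 30 in aim 3. This review proposes no duration.
2. For between-arm analyses at both 30 and 90 days, classify the PrEP and substance use treatment continuums from self-report and medical record. Classify linkage to other services from self-report alone, since no medical record is listed for that row.
3. Remove navigator report from the outcome sources for those analyses, and keep it as process data describing delivery in the intervention arm.

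The cost is a wording change to Table 1 and the analysis section, using sources already listed and no new data collection. The downside is that some steps known only to the navigator no longer count as outcomes, and linkage to other services rests on a single self-reported source.

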#### Recruitment and Randomization

Recruitment procedures will be informed by aim 2 results. Participants will be randomized either to the intervention group (n=50) or the standard of care (n=25) using a 2:1 randomization allocation scheme (Figure 2). Figure 3 provides a schematic of our study processes. Each participant will complete a baseline assessment immediately following the consent process. At the end of the baseline assessment, participants will be randomized to the intervention or control condition using a computerized algorithm programmed into REDCap (Research Electronic Data Capture; Vanderbilt University). Randomization will be blocked to avoid “runs” of assignment to the same.

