#### Standard of Care

The standard of care is a referral to substance use treatment and HIV prevention services from an individual’s case worker.

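### Navigator report is a source for three secondary outcomes compared between arms, but only the intervention arm has a navigator, so ascertainment differs by arm

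*Protocol article*

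**What the plan says.** Three rows of Table 1 in the protocol article, under Secondary outcomes, name the navigator as a source, each ticked at 30 and 90 days:

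- "Linkage to other services: self-report and Navigator report"
- "Substance use treatment continuum (accepted, initiated, and adhered): navigator report, medical record, and self-report"
- a parallel row for the PrEP continuum, built from the same three sources as the row just quoted

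Under Pilot Trial Outcomes, the navigator is said to track the prelinkage and downstream outcomes. The same paragraph describes substance use treatment linkage, a primary outcome, as attendance "verified by the navigator and medical provider collateral (if the participant agrees"). The Table 1 row for that outcome lists self-report and provider collateral and does not mention the navigator.

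The comparator is described in one sentence under Standard of Care: "The standard of care is a referral to substance use treatment and HIV prevention services from an individual’s case worker". Nothing in the text gives controls a navigator or a substitute reporter.

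Under Data Management and Analysis, logistic regression on condition is applied to the primary outcomes and "all other dichotomous outcomes (eg, acceptance of PrEP and substance use treatment referral"). The dependent variable is a yes/no summary over the month 1 and month 3 assessments of whether the outcome happened at any time.

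**The concern.** A comparison of event proportions between arms is fair only if an event has the same chance of being recorded in each arm. Here the intervention arm has a reporter that the control arm lacks. That reporter is the person who delivers the intervention, knows the allocation and, under the Aim 2 navigation protocol, initiates contact at least three times a week. Events that a participant forgets or does not mention at interview can reach the data through the navigator in one arm only.

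At stake is the reading of the affected odds ratios as evidence of preliminary impact, which the article says will contribute to a future trial. This kind of error does not shrink as the sample grows.

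**Working it through.** The plan gives no figure to reproduce for these outcomes. The only stated numbers are the arm sizes: "Participants will be randomized either to the intervention group (n=50) or the standard of care (n=25) using a 2:1 randomization allocation scheme". These agree with a total of 75 (75 × 2/3 = 50; 75 × 1/3 = 25).

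**Step 1: sources by arm, from the text.**

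| Outcome | Intervention arm | Control arm |
|---|---|---|
| Linkage to other services | self-report, navigator | self-report |
| Continua (PrEP, substance use treatment) | navigator, medical record, self-report | medical record, self-report |

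For the continua, the imbalance matters only where the shared sources miss events. A medical record may well not hold acceptance of a referral, so that step probably resembles the first row. Initiation and adherence are more likely to be recorded.

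**Step 2: a model with no true effect.** Let p be the true event rate, equal in both arms. Let s be the sensitivity of self-report and g the share of missed events that the navigator catches. An event counts if any source reports it, and there are no false reports. Then

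- control observed rate = p·s
- intervention observed rate = p·[1 − (1 − s)(1 − g)]
- spurious difference = p·(1 − s)·g

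All of p, s, g and the any-source rule are assumptions. The upper value of g is 0.70. The lower value, 0.35, supposes that half the events fall inside the 30-day navigation period given in the Aim 2 protocol (0.5 × 0.70 = 0.35).

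**Step 3: results.**

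| p | s | Control | Intervention, g = 0.35 | Difference (points), OR | Intervention, g = 0.70 | Difference (points), OR |
|---|---|---|---|---|---|---|
| 0.40 | 0.9 | 36.0% | 37.4% | 1.4, 1.06 | 38.8% | 2.8, 1.13 |
| 0.40 | 0.8 | 32.0% | 34.8% | 2.8, 1.13 | 37.6% | 5.6, 1.28 |
| 0.40 | 0.6 | 24.0% | 29.6% | 5.6, 1.33 | 35.2% | 11.2, 1.72 |
| 0.60 | 0.9 | 54.0% | 56.1% | 2.1, 1.09 | 58.2% | 4.2, 1.19 |
| 0.60 | 0.6 | 36.0% | 44.4% | 8.4, 1.42 | 52.8% | 16.8, 1.99 |

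The ends of the range are 0.40 × 0.1 × 0.35 = 1.4 points and 0.60 × 0.4 × 0.70 = 16.8 points. With the same sources in both arms (g = 0), the odds ratio is 1.00.

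**Step 4: direction under other combining rules.** If both self-report and navigator report were required, no control could have an event for linkage to other services, which again favours navigation. If navigator report were used to correct over-reported self-report, the sign could reverse. Assume self-report sensitivity of 0.9, a 10% false-report rate and a navigator who is always right. Controls then show 0.9p + 0.1(1 − p) against p in the intervention arm. At p = 0.2 this is 26% against 20% (−6 points); at p = 0.5 the difference is 0. Nothing in the text describes such a use.

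**The case against.** The strongest reply is that the article states no rule for combining sources, and that a condensed article may leave such a rule to the full protocol or analysis plan. This stands as far as direction and size go: both are conditional. It does not remove the point, because the listing of a one-arm source for outcomes compared by condition is stated in the article itself.

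A second reply is that the analysed indicators rest on the month 1 and month 3 assessments, which are interviews or web surveys described alike for both arms, so navigator tracking may be process data only. That reading is possible, but Table 1 ticks navigator report at both visits as an outcome source, so the article does not settle it.

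Third, both continuum rows also list medical record. This stands, and limits the clear case to one row.

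Three stronger readings are tempting and not supported:

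- A reader might infer that bias toward navigation is certain. It depends on an unstated scoring rule, although an any-source rule is the natural reading of an indicator that the event happened at any time.
- A reader might infer that an intervention participant who misses an assessment would be scored a success from the navigator's log. No section says so.
- A reader might infer that the upper figures are typical. They need the highest event rate and lowest sensitivity considered, and a 70% catch rate over the whole 90 days, although the only stated navigation period is 30 days.

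Nor can one say that the error would pass into the future trial, whose outcome definitions are not in the document.

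**Conclusion.** The point holds in conditional form. Ascertainment of three secondary outcomes differs by arm as written. If a report from any source counts, the comparison is biased toward navigation. Confidence is highest for linkage to other services and moderate for acceptance of referral; for initiation and adherence it depends on how complete the medical records are. The documents do not allow the size to be known. The illustrative range of roughly 1 to 17 points treats self-report as the only shared source, so it describes linkage to other services and, probably, acceptance.

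The consequence is limited: this is a 75-person pilot, and the article calls the downstream outcomes exploratory. PrEP linkage, verified by medical record, is not affected. For substance use treatment linkage, the text and Table 1 disagree on whether the navigator is a verifier, and they must be reconciled. The correction costs little and should be made.

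**What to change.** In Pilot Trial Outcomes, Table 1 and Data Management and Analysis:

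1. Define every outcome compared between arms only from sources collected identically in both: self-report to study staff at months 1 and 3, plus the medical or provider records already planned, sought for all randomised participants on the same schedule.
2. Take navigator report out of the between-arm definitions of the three Table 1 rows. Keep it as descriptive process data for the intervention arm, and add navigator-only events in a sensitivity analysis labelled as such.
3. Reconcile the text with Table 1 for substance use treatment linkage by removing the navigator as verifier in the between-arm definition.

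The cost is a change of wording and one extra table, with no new type of data. The downside is that some true intervention-arm events known only to the navigator leave the main comparison, so observed rates in that arm may be somewhat lower. The sensitivity analysis shows how many.
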